# Evaluation of implementation and effectiveness of neck-specific exercise for persistent disability and pain after whiplash injury: study protocol for a randomized controlled study using a hybrid 2 design

**DOI:** 10.1186/s12891-022-05470-y

**Published:** 2022-05-30

**Keywords:** Neck pain, Exercise, Whiplash injuries, Implementation science, Rehabilitation

## Abstract

**Background:**

Persistent pain and disability in whiplash-associated disorders (WAD) grades II and III are common. In two randomized controlled trials (RCTs) of neck-specific exercises (NSE), we have seen promising results in chronic WAD, with a sustained clinically important reduction in pain and disability. NSE can also be delivered through internet support (NSEIT) and a few visits to a physiotherapist, saving time and cost for both patients and providers. NSE have been shown to have positive effects in other neck pain disorders and we will evaluate the diffusion of the exercises to other patients. The aims of the proposed study are to evaluate an implementation strategy for NSEIT and NSE in primary health care and to evaluate the effectiveness of NSEIT and NSE in clinical practice.

**Methods:**

The proposed study is a prospective cluster-randomized mixed-design study with hybrid 2 trial design. Reg. physiotherapists working in twenty physiotherapy clinics will be included. The primary implementation outcome is proportion of patients with neck pain receiving neck-specific exercise. Secondary outcomes are; physiotherapists attitudes to implementation of evidence-based practice, their self-efficacy and confidence in performing NSEIT/NSE, number of patients visits, and use of additional or other exercises or treatment. To further evaluate the implementation strategy, two qualitative studies will be performed with a sample of the physiotherapists. The primary outcome in the patient effectiveness evaluation is self-reported neck disability according to the Neck Disability Index (NDI). Secondary outcomes are pain intensity in the neck, arm, and head; dizziness; work- and health-related issues; and patient’s improvement or deterioration over time. All measurements will be conducted at baseline and at 3 and 12 months. Physiotherapists´ self-efficacy and confidence in diagnosing and treating patients with neck pain will also be evaluated directly after their instruction in NSEIT/NSE.

**Discussion:**

This trial will evaluate the implementation strategy in terms of adoption of and adherence to NSEIT and NSE in clinical primary health care, and measure diffusion of the method to other patients. In parallel, the effectiveness of the method will be evaluated. The results may guide physiotherapists and health care providers to sustainable and effective implementation of effective exercise programs.

**Trial registration:**

The randomized trial is registered on ClinicalTrials.gov, NCT05198258, initial release date January 20, 2022.

## Background

There is usually a considerable time lag from results in health research to implementation and use in clinical practice. Time to implementation is commonly reported to be up to 20 years [1]. For patients suffering from disorders, such as persistent whiplash-associated disorders (WAD), for which treatments until recently have been inconclusive, fast implementation of new effective methods is crucial. Years after whiplash trauma, persistent pain and disability affect up to 50% of those injured [2], and 30% will experience severe symptoms [3]. No evidence is currently available regarding invasive interventions [4]; exercise and patient education are recommended [5], but only modest effects have been demonstrated [6, 7]. Results from a randomized controlled study (RCT) of neck-specific exercises (NSE) showed promising results in chronic WAD, with a sustained clinically important reduction in pain and disability [8]. NSE supervised by a physiotherapist twice weekly for 3 months was superior to prescribed physical activity [9, 10] and better than staying on a waiting list for individuals with chronic WAD [11]. The NSE group showed up to 50% pain reduction and improvement in disability [10], with sustained improvement 2 years after the exercise intervention [8]. In a recent RCT, NSE was compared with an internet-based neck-specific exercise program (NSEIT) that consists of the same information and exercises as the NSE [12] but includes only four visits to the physiotherapist. Although participants had chronic WAD, both groups significantly improved (unpublished results, manuscript under review), and the internet-based intervention was non-inferior to NSE. The results thereby confirm the good results of the earlier RCT [8]. A broad implementation of this method in primary care would give patients with WAD a flexible method with which to improve function and health and decrease pain. NSEIT is also less time consuming and less expensive for the health care system.

### Implementation strategies

Several theories, frameworks, and taxonomies to promote and facilitate the uptake of evidence in practice are currently available [13, 14]. Nonetheless, theory-based efforts to implement new methods into practice have had meager results, often with no or small differences compared with controls [15, 16]. This highlights the complexity of changing health care providers’ and patients’ behavior and their attitudes towards the use of new methods. A clearly defined strategy involving different steps in the complex implementation process could overcome implementation resistance and facilitate knowledge translation [17, 18]. To succeed in implementing new evidence-based methods, it is important to understand the factors that hinder versus promote uptake of the new method [19]. This includes the individuals’ environment: for example, institutional factors (leaders) and public policy [20]. The diffusion-of-innovation theory [21] describes a behavioral change model for understanding and promoting the uptake of “an idea, practice or object that is perceived as new by an individual” and the process “by which an innovation is communicated through certain channels over time among the members of a social system”. Building on this theory, key determinants of diffusion speed and extent have been identified by Glanz et al. [22]. To succeed, the new method should be better than the current one, fit the intended audience, be easy to use, provide observable and easily measurable results, be adoptable with minimal investment in time, and have minimal risk and uncertainty [22]. When a comprehensive facilitation method was used to implement a behavioral medicine approach in primary care, the physiotherapists’ efficacy in using the method increased, but the initial change in clinical action was not maintained at the 3-, 6-, or 12-month follow-up [16]. The conclusions were that intrinsic motivation and continued support are important factors in maintaining behavioral changes [16]. Lack of time and heavy workloads in primary care may also make it difficult to implement complex methods.

In a prior study, NSE was implemented in primary care [23]. A one-day instructional program containing interactive components, which was earlier shown to give better results compared with only didactic education [24], was provided. After the instruction, physiotherapists (87%) reported that they used neck-specific exercises in WAD with significantly higher confidence than before, and these results were sustained at the one-year follow-up [23]. Suggestions for further improving the implementation were to arrange a follow-up session for repetition, or to divide the instruction between two occasions. A limitation of the study was that data were collected only at the group level, so it was not possible to evaluate change on an individual basis. The effectiveness of NSE in clinical practice, including the physiotherapists’ fidelity to the exercise program, was not evaluated and needs to be investigated further.

In implementing interventions, there are several factors that must be considered. One factor is how the characteristics of the intervention are perceived by the potential adopters, and if they see a relative advantage in comparison with current practice [22]. Individuals with persistent WAD are difficult to rehabilitate, they are high consumers of health care services [25], and effective treatment is lacking, which may enhance physiotherapists’ willingness to use the method [6, 7, 26, 27]. There is growing evidence that NSE has a significant effect in chronic whiplash-associated disorders (WAD), including in patients with severe symptoms (neurological signs) after the injury [8, 28]. The internet-based version NSEIT could further facilitate its applicability in the busy and complex setting of primary health care. Moreover, the NSEIT and NSE program is not considered a complex intervention and may therefore be easy to implement in clinical practice.

Education is an important component of implementation strategies, but a comprehensive strategy including many meetings with a facilitator has been found to be too time consuming [29]. In the present study the educational sessions will be limited in time to fit the busy physiotherapists’ workloads and will include mixed interactive and didactic components to enhance their effectiveness [24].

### RE-AIM framework

The RE-AIM framework was developed to identify and evaluate a broad aspect of important factors to translate research results into clinical practice [30, 31]. The five RE-AIM dimensions are Reach (R), Effectiveness (E), Adoption (A), Implementation (I), and Maintenance (M). The five dimensions relate both to the individual (R, E, and M, in the present study to patients with neck pain) and to staff and settings (A, I, and M). The RE-AIM framework [30, 31] will be used to evaluate the implementation strategy in the present study.

### Research needs

In randomized controlled trials, the intervention follows a strict protocol directed to a specific diagnosis and excludes other treatments or exercise intervention during the study period. This is important in evaluating its effectiveness—that is, whether the method is delivered as intended and has the same effect as in the RCTs [8, 12]. NSEIT and NSE have been evaluated in patients with chronic WAD [8, 12], but in clinical practice physiotherapists may use the method in patients with other neck pain disorders. To our knowledge this has not been investigated before, either for chronic WAD as a neck-specific exercise program or as an Internet-based exercise program. There are gaps in our knowledge regarding the best way to implement new exercise methods in primary care and whether or not the method will be used as intended and/or if the implemented method, in this case neck-specific exercises, will be used in patients with other neck pain disorders. Therefore, the proposed study will evaluate both the implementation strategy and the effectiveness of the implemented method in clinical practice [32].

### Aims and research question

The aims of the proposed study are to evaluate an implementation strategy for NSEIT and NSE in primary health care and to evaluate the effectiveness of the programs in clinical practice.

These research questions will be investigated according to the RE-AIM framework:Reach: To what extent do patients with WAD receive NSEIT/NSE in primary care?Effectiveness: Is the NSEIT/NSE program effective at decreasing disability and pain in patients with WAD or non-specific neck pain in primary care? Will the results be the same as in the RCTs at 3 and 12 months of follow-up?Adoption: To what extent do the physiotherapists apply the NSEIT/NSE for patients with WAD or non-specific neck pain?Implementation: To what extent is the intervention delivered according to the NSE protocol (fidelity)?Maintenance: To what extent will physiotherapists continue to use NSEIT/NSE at 12 months of follow-up?

## Method

### Design

We propose a prospective cluster-randomized mixed-design study evaluating the implementation strategy and effectiveness of the NSEIT/NSE. The study is based on hybrid 2 trial design, as described by Curran et al. [33], where both implementation and clinical effectiveness are tested simultaneously. This study has been approved by the Swedish Ethical Review Authority (Dnr: 2021-03383, 2021-06016-02, 2022-00479-02) and will be conducted in accordance with the Declaration of Helsinki.

### Participants and settings

Twenty physiotherapy clinics in primary health care in Sweden will be included. Twenty-five patients with neck pain will be consecutively recruited from each clinic, for a total of 500 patients. The flow diagram can be seen in Fig. 1 and the planned schedule of enrollment, interventions, and assessments in Fig. 2.

**Fig. 1 Fig1:**
[figure not shown]
Consort flow diagram

**Fig. 2 Fig2:**
[figure not shown]
Planned schedule of enrollment, interventions, and assessments

#### Inclusion criteria, implementation evaluation

Physiotherapy clinics in primary health care with ≥3 registered physiotherapists working at the clinic.

#### Exclusion criteria, implementation evaluation

No exclusion criteria for registered physiotherapists in the clinics that are recruited in the study.

#### Inclusion criteria, effectiveness evaluation

The physiotherapists will include patients ≥18 years old with neck pain. Patients will be required to have internet access by phone, tablet, or computer, be able to read and understand Swedish, and be interested in participating in the study.

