#### Exclusion criteria

Physiotherapists should exclude patients with “red flags”: symptoms that suggest a serious illness or spinal abnormality, including serious trauma to the neck and no X-ray, preceding neck surgery, osteoporosis, myelopathy, history of cancer, unexplained weight loss, current fever, history of infections, constant and progressive non-mechanical pain, insidious progression of pain, signs of spinal cord compression (neurological examination to exclude spinal cord or cervical myelopathy such as clumsy hands, altered gait, or disturbances in sexual, bladder, or sphincter function).

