### Recruitment of physiotherapy clinics and patients

In the first step, physiotherapy clinics will be recruited through contact with health care providers and research coordinators in county councils in Sweden. In the second step, an oral on-line presentation describing the study will be given to those health care providers that express interest in the study. If the eligible physiotherapy clinic confirms participation via e-mail after the presentation, physiotherapists will be included after written informed consent. Registered physiotherapists working at the included physiotherapy clinics will screen patients for eligibility by taking a detailed medical history and careful clinical examination, following the regulations for registered physiotherapists in Sweden (Health and Medical Services Act 2017:30 [36] and the patient security law (SFS 2010: 659. Patientsäkerhetslag. Stockholm: Socialdepartementet) [37]. Patients with neck pain deemed to benefit from the NSE or the NSEIT and who are willing to participate in the study will be included. If the eligible patient confirms participation, written and informed consent will be completed through Health Care Guide 1177 (a national hub for health care information and services in Sweden) and patients logging in using BankID. Before completing the consent form, potential participants (physiotherapists and patients) will read the information, describing the purpose of the study, data collection process, duration of commitment, intervention, and benefits and harms of the treatment. The information also explains that participants can withdraw from participation at any time of the study. Patients are insured by the County Council Mutual Insurance Company, a mutual insurance company that covers patient injury (compensation to those who suffer harm) for all public health care providers and private providers contracting with the Swedish government.

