#### The effectiveness of NSEIT/NSE

Background data will be collected, including age, sex, symptom duration, and whiplash injury or other reason for neck pain.

The primary outcome measure that will be collected is neck-specific function as measured by the Neck Disability Index (NDI) [42].

The secondary outcome measurements will be pain intensity (current, average last week, worst pain last week) in the neck, head, and arm, and dizziness (current, average last week, worst dizziness last week) in the past week, using a numeric rating scale (NRS, score 0 to 10: 0 = no pain or dizziness, 10 = worst imaginable pain or dizziness) [43]; answers to questions about health-related quality of life; work ability measured with the Work Ability Score (WAS) reporting “current work ability compared to highest work ability ever” (score 0 to 10; 0 = cannot work at all, 10 = best work ability [44]; and patient’s improvement or deterioration over time, measured with an 11-point global rating scale (GRS: − 5 = vastly worse, 0 = unchanged, 5 = completely recovered) [45]. Any adverse events or negative effects will be registered at the 3-month follow-up.

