### Statistical analyses

All analyses will be conducted in collaboration with a statistician. Data will be analyzed according to intention to treat and supplemented with per protocol analysis. An analysis will be done of the missing data. Imputation methods may be used when deemed to have additional value. Subgroup analyses of age, gender, neck pain intensity, headache, and dizziness may possibly be performed.*Data regarding the implementation strategy* will be analyzed using a parametric t-test and a linear mixed model or repeated-measures ANOVA or the non-parametric Mann-Whitney U test and Kruskal-Wallis test, depending on the data. Analyses will evaluate differences between groups A and B and changes in variables over time.*Data regarding the effectiveness of NSEIT and NSE* will be analyzed with a linear mixed model or repeated-measures ANOVA or Kruskal-Wallis, depending on the data. NDI, pain intensity, headache, and dizziness will be evaluated as dependent variables with time as an independent fixed factor (baseline, 3 months, and 12 months after start of intervention). The results will be compared with the results from the RCT studies [8, 12].

The effect of neck-specific exercises in the present study for WAD grades II and III and for patients with other neck-pain disorders will also be evaluated and compared with the results in the RCT studies [8, 12].

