## Discussion

Neck-specific exercises have been evaluated in two RCTs, showing reduced disability and neck pain in individuals with persistent WAD [8, 9, 12]. Access to internet-based treatment can shorten waiting time, enhance availability, and reduce costs. NSEIT was noninferior to NSE, and the exercise program can be delivered via internet with fewer visits to health care. The next step will be to implement NSEIT among physiotherapists in primary care. This pragmatic project is based on the RE-AIM framework and diffusion-of-innovation theory. At the staff and setting levels, our intent to evaluate the approach’s reach (the proportions of patients receiving NSEIT/NSE), and the adoption, implementation, and maintenance of the method. At the patient level, we plan to evaluate the effectiveness of NSEIT/NSE for patients with persistent WAD, the diffusion of NSEIT/NSE to other patients with neck pain, and the maintenance of results (long-term effectiveness). The project is important because it will increase our understanding of the factors that will promote implementation of NSEIT/NSE in primary care and because it will evaluate the effectiveness of the method. Results from this study will bridge the gap between research and clinical practice and guide large-scale implementation of NSEIT/NSE.

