### Limitations

The limitations of the present study are related to the pragmatic approach. To study the implementation process and the adoption, diffusion, and maintenance of the NSEIT/NSE in clinical practice we could not follow as strict a protocol as in an RCT, which means we have less control over the study. The physiotherapists will select patients whose condition they have deemed to be improved by neck-specific exercises. Because all patients will be evaluated as one group, with no comparison with other treatments or exercise methods, threats to internal validity exist; that is, threats to confidence that the results are trustworthy. However, we will compare the results with the findings in our previous RCTs. Threats to the study’s external validity arise from the fact that only neck-pain patients and physiotherapy clinics that are interested in participating in the study will be evaluated. With these concerns in mind, the results can be generalized to physiotherapy clinics in primary care, as many different regions and physiotherapy clinics will participate in the study.

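### Neck pain of any duration is eligible, yet the one-group NDI change is compared with RCTs in chronic WAD without matching on symptom duration

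*Protocol article*

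**What the plan says.** **Who enters.** The section on inclusion criteria for the effectiveness evaluation states: "The physiotherapists will include patients ≥18 years old with neck pain". It adds internet access, Swedish and interest in taking part. Recruitment of physiotherapy clinics and patients adds a clinical judgement: "Patients with neck pain deemed to benefit from the NSE or the NSEIT and who are willing to participate in the study will be included". Exclusions concern serious pathology: "Physiotherapists should exclude patients with “red flags”: symptoms that suggest a serious illness or spinal abnormality". None of these sections sets a minimum or maximum symptom duration.

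**What is recorded.** Under The effectiveness of NSEIT/NSE: "Background data will be collected, including age, sex, symptom duration, and whiplash injury or other reason for neck pain".

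**How effectiveness is judged.** Statistical analyses models NDI with time (baseline, 3 and 12 months) as the fixed factor. Sample size says that exercise recipients from both randomised groups are pooled for this purpose. Limitations concedes that there is no comparison treatment and then offers: "However, we will compare the results with the findings in our previous RCTs". Research needs describes those RCTs as trials in chronic WAD.

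**Splits foreseen.** Statistical analyses also plans to evaluate WAD grades II and III and other neck-pain disorders and to compare the results with the RCTs. On further subgroups: "Subgroup analyses of age, gender, neck pain intensity, headache, and dizziness may possibly be performed". Duration is not listed.

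**Stated target.** The title refers to persistent complaints after whiplash injury. The Discussion names as a patient-level aim "the effectiveness of NSEIT/NSE for patients with persistent WAD".

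**The concern.** One research question is whether results in routine care will match those of the RCTs at 3 and 12 months. That requires patients who resemble the RCT patients in whatever drives NDI change without treatment, and symptom duration is an obvious candidate. A patient injured a few weeks ago is eligible here but falls outside a chronic-WAD population.

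In a one-group model with time as the only named factor, spontaneous improvement and the effect of exercise enter the same coefficient. If recent-onset patients make up a material share, their recovery adds to the fall in NDI. The result could then look like the RCTs although the exercise did less in practice, or differ from them for reasons of case mix alone. The WAD II/III subset does not settle this, since it too may contain recent injuries. At stake is the reading of the effectiveness question, not the randomised comparison of implementation strategies.

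**Working it through.** **1. The plan's own figure.** Sample size gives f = 0.2 (d = 0.4), correlation 0.3, 80% power, alpha 0.05 and 56 participants. A one-group repeated-measures F test with three time points and noncentrality f²·n·3/(1 − 0.3) needs n = 58 and has power 0.787 at n = 56. This agrees closely with the stated figure. Then 56/(1 − 0.20) = 70, as stated. The sample size is not in dispute.

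**2. Scale.** A 7-point improvement at d = 0.4 implies SD = 7/0.4 = 17.5. With correlation 0.3, the SD of change = 17.5 × √(2 × (1 − 0.3)) = 20.7.

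**3. Drift without any exercise effect.** Let q be the share of recent-onset patients and x their spontaneous NDI fall. Mean drift = q × x. The protocol gives neither value, so both are assumptions:

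- q = 10%, x = 5: 0.5 points, or 7% of the 7-point criterion.
- q = 30%, x = 10: 3.0 points, or 43%.
- q = 30%, x = 20: 6.0 points, or 86%.

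The drift does not depend on the number analysed, so more patients do not reduce it.

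**4. How many are analysed.** Three values bracket what the Sample size section allows:

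- 56, the planned number.
- 400, if all 500 count, less 20% dropout.
- About 130, if only exercise recipients count and the assumed rates of 25% and 40% apply to the 500: 500 × (0.25 + 0.40)/2 ≈ 163, and 163 × 0.8 ≈ 130.

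**5. Chance that the drift alone is significant.** SE = 20.7/√n. The two-sided 5% probability is Φ(drift/SE − 1.96) + Φ(−drift/SE − 1.96), for a baseline-to-follow-up paired test:

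| n | SE | drift 0.5 | drift 3 | drift 6 |
|---|---|---|---|---|
| 56 | 2.77 | 5% | 19% | 58% |
| 130 | 1.82 | 6% | 38% | 91% |
| 400 | 1.04 | 8% | 83% | >99% |

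With few recent-onset patients and little recovery, almost nothing happens. With a moderate share and marked recovery, the drift approaches the plan's own criterion.

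**6. Does any stated analysis separate the two?** Eligibility does not, the model has no duration term, the diagnostic split is not by duration, and duration is absent from the possible subgroups. It is recorded at baseline, so the separation is feasible.

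**The case against.** **Broad entry is intended.** The effectiveness question in Aims and research question covers WAD or non-specific neck pain without a duration limit, and diffusion to other neck-pain patients is an explicit aim. This stands: the inclusion criteria fit that question and need not change. It does not rescue the comparison with chronic-WAD trials, which needs a comparable set.

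**The weakness is disclosed.** Limitations admits the single group, the physiotherapists' selection of patients and threats to internal validity. That is fair, but it mentions neither duration nor natural recovery, and it relies on the very comparison that duration undermines.

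**The analysis plan may handle it.** Covariates and further detail can sit in a document not shown, so one can say only that the article names no use of duration. The article does, however, itself fix the pooled group, the time-only factor, the external comparator and the diagnostic split.

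Three stronger readings are tempting and not supported:

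- A reader might infer that natural recovery will in fact account for the result. The share of recent-onset patients and their recovery are not in the documents. The Background figure of persistent symptoms in up to half of those injured concerns everyone injured, years later, not patients who seek physiotherapy and are judged likely to benefit.
- A reader might infer that co-treatment, allowed here, was barred in the two benchmark RCTs. The sentence in Research needs is about randomised trials in general; it does not state those trials' rules.
- A reader might infer that WAD grade goes unrecorded. The background list is not presented as exhaustive, and the planned WAD II/III evaluation presupposes that grade is known.

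**Conclusion.** The point holds as a mismatch between an any-duration cohort and a chronic-WAD benchmark, which no analysis stated in the article resolves. Agreement or disagreement with the RCTs could partly reflect case mix. The size cannot be determined from the documents: under the assumptions above, the drift runs from a negligible 0.5 points to 3 to 6 points against the 7-point criterion. The significance probabilities rest further on the implied SD of 17.5, the correlation of 0.3 and an uncertain number analysed.

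This does not show that the effectiveness aim must be confined to chronic WAD. That would change the research question, and the result would still be an uncontrolled before-after change. The change is worth making because it reduces bias in a question the trial itself asks, using a variable already collected.

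**What to change.** Leave eligibility, the randomised comparison and the all-comers analysis as they are, and prespecify the following:

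1. The comparison with the RCTs uses patients with WAD grades II/III who meet the RCTs' own symptom-duration criterion, applied to the duration recorded at baseline. The article does not give that cut-off, so it should be stated.
2. NDI results are reported by duration (recent-onset versus persistent), separately for WAD and for other neck pain.
3. The all-comers result is worded as change over time, not as an effect of the program.

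A sensitivity analysis leaving out patients with recorded co-treatment is optional.

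**Cost.** Mainly wording, plus confirmation that WAD grade is captured at baseline. The RCT comparison will have fewer patients and less precision. The plan needs 70 participants for the effectiveness aim, and nothing in the protocol assures 70 exercise-treated patients with chronic WAD II/III. The matched set improves comparability with the RCTs but does not remove regression to the mean or supply a concurrent control, and the report should say so.
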